## Abstract

**Background:**

Although gaming is a common arena where children socialize, an increasing number of children are exhibiting signs of problem gaming or internet gaming disorder. An important factor to the development of problem gaming is parent-child relationships. A cognitive behavioral therapy–based form of treatment, labeled relapse prevention, has been developed as a treatment for child and adolescent problem gaming or internet gaming disorder. However, no study has evaluated the effect of this treatment among Swedish children and youth nor the role of the parent-child relationships in this treatment.

**Objective:**

This study aims (1) to evaluate a relapse prevention treatment for patients showing signs of problem gaming or internet gaming disorder recruited from child and youth psychiatric clinics and (2) to test whether the quality of parent-child relationships plays a role in the effect of relapse prevention treatment and vice versa—whether the relapse prevention treatment has a spillover effect on the quality of parent-child relationships. Moreover, we explore the carer’s attitudes about parent-child relationships and child gaming, as well as experiences of the treatment among the children, their carers, and the clinicians who carried out the treatment.

**Methods:**

This study is a 2-arm, parallel-group, early-stage randomized controlled trial with embedded qualitative components. Children aged 12-18 years who meet the criteria for problem gaming or internet gaming disorder will be randomized in a 1:1 ratio to either intervention (relapse prevention treatment) or control (treatment as usual), with a total of 160 (80 + 80) participants. The primary outcomes are measures of gaming and gambling behavior before and after intervention, and the secondary outcomes include child ratings of parent-child communication and family functioning. The study is supplemented with a qualitative component with semistructured interviews to capture participants’ and clinicians’ experiences of the relapse prevention, as well as attitudes about parent-child relationships and parenting needs in carers whose children completed the treatment.

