### Recruitment and Eligibility

The trial and the recruitment will be carried out in several outpatient child and youth psychiatric clinics in Region Skåne in southern Sweden. As part of routine practice, all children (ages 12-18 years) coming for their first visit to 4 child and youth psychiatric units in Region Skåne will be screened for gaming or gambling behaviors. Children will be eligible to be included in the trial if they are aged 12-18 years and referred to outpatient child and youth psychiatric clinics in Region Skåne, meet criteria for problem gaming and internet gaming disorder, and have capacity to provide written informed consent. Children below the age of 15 years need to have their caregivers’ consent. Children will be excluded if they do not speak Swedish. The clinicians who meet children during their first visit to the child and youth psychiatric unit will inform and invite the eligible children to participate in the study.

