### Intervention

There is at this time a lack of consensus regarding treatment methods for problem gaming [22], in part due to a lack of clinical research [23]. However, together with 4 experienced psychologists in the field, we developed a manual drawing on previous knowledge in the field of addiction and the field of child and adolescent psychiatric treatment. Relapse prevention for alcohol and substance abuse was used as a theoretical underpinning [20] to develop a manual with 2 aspects in mind: adapting the blurbs and examples for children and adolescents—in part by including a fictionalized adolescent when demonstrating the theme of the particular session; and by structuring the sessions so that they could be easily adapted to fit the participant’s primary problem behavior—gaming or gambling. Patients who meet the criteria for disordered gambling or gaming (according to tentative criteria from the DSM-5) will be offered the opportunity to participate in a relapse preventive treatment intervention at their local clinic or where applicable at an adjacent clinic. The treatment will be administered in an individual format and consist of 7 to 9 sessions of 45 minutes over a period of 7 to 9 weeks. The treatment will be offered to participants both in person and via video link to facilitate participation for children and adolescents living further away from the participating clinics.

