### Sample Size

Patients who have agreed to participate in the treatment study will be randomized in a 1: 1 ratio between intervention and control group. In our power calculation, we estimated that 40% in the intervention group and 20% in the control group will see improvement through the treatment offered in different groups, and after this treatment fall under the cutoff for problem gaming. With these figures, 160 (80 + 80) patients must be included in the treatment study for us to be able to demonstrate a significant difference with sufficient power. Given the large number of patients in pediatric and youth psychiatry in the region and the likely high incidence of problem behaviors in the population, we believe it is possible to reach this number of participants in the study.

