### Measures and Data Collection

Background information, including gender, age, housing situation, and diagnosis, as well as primary outcome measures assessing gaming and gambling problems, will be collected via the platform “Blå appen” (“Blue application” in Swedish). Blå appen is a digital platform developed by the child and youth outpatient department in Region Skåne, distributing and summarizing online self-rated questionnaires. It is used throughout Swedish child and youth psychiatry to facilitate the usage of self-rated questionnaires to patients. The secondary outcome measures, including parent-child communication and connectedness and family climate, will be administered in paper format after the child has provided consent to the study. Because the secondary outcomes measures assess general parent-child interactions, specific questions about gaming will also be added. The patients who consent to the RCT will rate their gaming and gambling activity as well as their parent-child relationships before and after the treatment. The “treatment at usual” arm will do the rating of gaming and gambling activity as well as their parent-child relationships at the inclusion and 3 months after the inclusion to the study. The following primary outcome measures will be used:

The Game Addiction Scale for Adolescents [24] applies to gaming behavior during the previous 6 months based on 7 items. Each question covers one criterion in the DSM-5, answered on a 5-point Likert scale ranging from 1 (never) to 5 (very often) and should according to the developer be counted as endorsed when rated 3 or higher.The Diagnostic Screen for Gambling Problems–Control, Lying, and Preoccupation (NODS-CLiP) [25] is the shorter form of the NODS [26], which assesses gambling problems. NODS yield a score ranging from 0 to 10, corresponding to the DSM-4 criteria for gambling, where a score of 5 or more qualifies as pathological, a score of 3-4 corresponds to the subclinical syndrome of problem gambling, and scores of 1-2 corresponds to an “at-risk” status. NODS-CLiP comprises the 3 NODS items that best describe problem gambling, with 3 NODS questions pertaining to loss of Control, Lying, and Preoccupation—the “CLiP.”

The following secondary, somewhat adapted, outcome measures will be used:

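### A gaming scale and a 3-item gambling screen are unranked primary outcomes, but the objectives and the sample size concern gaming only

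*Protocol article*

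**What the plan says.** The abstract (Methods) speaks of primary outcomes in the plural: "The primary outcomes are measures of gaming and gambling behavior before and after intervention". Under Measures and Data Collection, the sentence "The following primary outcome measures will be used" introduces two instruments: the 7-item Game Addiction Scale for Adolescents and NODS-CLiP. Neither is placed above the other.

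On the gambling instrument, the same section says "NODS yield a score ranging from 0 to 10" and gives three bands for that parent scale: 1-2 at risk, 3-4 problem gambling, 5 or more pathological. It then says "NODS-CLiP comprises the 3 NODS items that best describe problem gambling". No threshold is given for the 3-item form.

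Under Aim and Objectives, the RCT objective is effectiveness on problem gaming and internet gaming disorder, and gambling appears in none of the listed objectives. Under Sample Size, the assumed success is that patients "after this treatment fall under the cutoff for problem gaming", with 40% v 20% and 80 + 80 patients.

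The population is described in two ways. Under Recruitment and Eligibility, children must "meet criteria for problem gaming and internet gaming disorder, and have capacity to provide written informed consent". Under Intervention: "Patients who meet the criteria for disordered gambling or gaming (according to tentative criteria from the DSM-5) will be offered the opportunity to participate".

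**The concern.** The choice and rank of the primary outcomes belong in the protocol, because they determine what a positive trial means. Here one of the two primaries matches the objectives and the sample size, and the other matches neither. A reader cannot tell whether the trial succeeds on gaming alone, on either outcome, or only on both. The either-outcome reading raises the false positive rate. The both-outcomes reading ties the result to a measure with no power calculation. Leaving the choice open until results are known would weaken the main claim, even if the gaming result is sound.

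Two features of the gambling measure add to this. If children enter on gaming criteria only, many may have little gambling to reduce. And the only score bands printed belong to a longer scale.

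**Working it through.** **Inputs.** From Sample Size: 40% v 20%, 80 per arm. From Randomization: 1:1 allocation. The article states neither alpha nor power as a number. I assume two-sided 5%, in line with the 95% CIs under Statistical Analysis, and 80% power. The article gives no rate of gambling at baseline, so I show a range.

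**1. The plan's own figure, for gaming.** The mean proportion is (0.40 + 0.20)/2 = 0.30.

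- Pooled formula: n = [1.960·√(2·0.30·0.70) + 0.842·√(0.40·0.60 + 0.20·0.80)]² / 0.20² = 81.2, so 82 per arm (164).
- Unpooled formula: n = (1.960 + 0.842)²·(0.24 + 0.16)/0.04 = 78.5, so 79 per arm (158).
- Power at 80 per arm: SE under the null = √(2·0.30·0.70/80) = 0.07246; SE under the alternative = √(0.24/80 + 0.16/80) = 0.07071; z = (0.20 − 1.960·0.07246)/0.07071 = 0.820; power = 79.4%.

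The stated 160 therefore reproduces for the gaming endpoint. It contains nothing for gambling.

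**2. If success on either outcome counts.** With two independent tests at 5%, the family-wise error is 1 − 0.95² = 9.75%. The Bonferroni bound, which needs no assumption about dependence, is 10%. With correlated normal test statistics it is 9.1% at a correlation of 0.5 and 7.0% at 0.9.

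If gambling is rare, its own test rejects less often than 5% under the null. Take a binary screen, 80 per arm, the same positive rate in both arms, and independence from the gaming test. The family-wise error is 1 − 0.95·(1 − r), where r is the actual rejection rate of the gambling test:

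| Gambling-positive rate | r, pooled z-test | Family-wise error, pooled z | Family-wise error, Fisher |
|---|---|---|---|
| 1% | 0.8% | 5.7% | 5.0% |
| 2% | 3.1% | 8.0% | 5.2% |
| 5% | 4.2% | 9.0% | 6.5% |

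**3. If both must succeed.** The error rate does not rise, but joint power cannot exceed the power of the gambling test. Suppose a share q of children is gambling-positive at baseline, 40% v 20% of them resolve, and nobody becomes newly positive. The positive rates after treatment are then 0.6q and 0.8q. With the same power formula and 80 per arm:

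| q (assumed) | Rates compared | Power, all 80 per arm | Power, baseline positives only |
|---|---|---|---|
| 10% | 6% v 8% | 7% | 13% (8 per arm) |
| 20% | 12% v 16% | 11% | 23% (16 per arm) |
| 50% | 30% v 40% | 26% | 50% (40 per arm) |
| 100% | 60% v 80% | 79% | 79% (80 per arm) |

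For q = 10%: the mean rate is 0.07, SE under the null = √(2·0.07·0.93/80) = 0.0403, and z = (0.02 − 1.960·0.0403)/0.0403 = −1.465, so power is 7.1%. The last column is a normal approximation, and it is generous in the small groups.

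**4. The score bands.** A count of three yes/no items runs from 0 to 3. On that range a score of 5 or more cannot occur, and the 3-4 band would mean endorsing all three items. The parent-scale bands therefore cannot serve as a threshold for NODS-CLiP.

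**The case against.** The strongest defence has four parts.

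**Gaming plainly leads.** The objectives and the sample size both point to gaming, and this is an early-stage trial. A success rule or a division of alpha is commonly left to an analysis plan, which is not shown. This stands in part. I do not count the absence of a multiplicity rule as a fault. The defect is that the article itself labels as primary a measure that its own objectives and sample size leave out.

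**The floor effect is unproven.** A reader might infer that most children will score 0 on NODS-CLiP and cannot improve. The article gives no gambling rate. It screens for gaming or gambling, mentions in the Background that the two may occur together, and under Intervention offers treatment to patients with disordered gambling or gaming. A floor is likely only if the gaming-only eligibility statement governs.

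**The inflation can be overstated.** A reader might say that a second primary doubles the false positive rate. That holds only approximately, with an either-outcome rule that the article never states and with independent tests. It also sits badly with a floor effect: the rarer gambling is, the smaller the inflation. A loss of gaming power from splitting alpha is likewise no consequence of this plan, since no split is proposed.

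**The bands are not misapplied.** The text assigns the 0-10 range to the full NODS and does not say that it scores NODS-CLiP. This stands. It would be wrong to say that the plan uses an unreachable cutoff, or that no cutoff for the 3-item form exists. The article simply states none.

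**Conclusion.** The point holds in this limited form and should be fixed. Two unranked primary outcomes are listed, while the objectives and the 160-patient calculation cover gaming only.

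The size depends on how success is defined. Under an either-outcome rule, the family-wise error is about 9.75% with independent tests at 5%, and lower with correlation or rare gambling. Under a both-outcomes rule, power is held to about 7% to 26% when 10% to 50% of children are gambling-positive at baseline, comparing full arms. Even restricted to baseline positives it is no more than about 50% at a share of 50%. With gaming as the only primary, 80 per arm keeps about 79% power at the full 5%.

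These figures rest on an assumed two-sided 5% level, on assumed gambling shares, and on borrowing the 40% v 20% gaming rates for gambling.

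**What to change.** - Name one primary outcome: the proportion falling under the problem gaming cutoff on the Game Addiction Scale for Adolescents, matching Sample Size. Use the same wording in the abstract and under Measures and Data Collection.
- Make NODS-CLiP secondary or descriptive, reported on its own 3-item range. State that the printed 0-10 bands describe the parent scale only.
- Reconcile Recruitment and Eligibility with Intervention on whether disordered gambling alone allows entry. This bears on the first change, because a child who enters for gambling alone may already be under the gaming cutoff at baseline and could not count as improved on it.
- If both outcomes are to stay primary, state the success rule, how the error rate is kept at 5%, the NODS-CLiP scoring, and its power.

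The change should be dated, and made before outcomes are compared between arms. The cost is wording in the protocol, and in the registry entry if that lists both outcomes; no extra patients are needed. The downside is that no confirmatory claim on gambling can be made.

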**Results:**

The trial started in January 2022 and is expected to end in December 2023. The first results are expected in March 2023.

**Conclusions:**

This study will be the first randomized controlled trial evaluating relapse prevention as a treatment for child and adolescent problem gaming and internet gaming disorder in Sweden. Since problem behaviors in children interact with the family context, investigating parent-child relationships adjacent to the treatment of child problem gaming and internet gaming disorder is an important strength of the study. Further, different parties, ie, children, carers, and clinicians, will be directly or indirectly involved in the evaluation of the treatment, providing more knowledge of the treatment and its effect. Limitations include comorbidity in children with problem gaming and internet gaming disorder and challenges with the recruitment of participants.

**Trial Registration:**

ClinicalTrials.gov NCT05506384 (retrospectively registered); https://clinicaltrials.gov/ct2/show/NCT05506384

**International Registered Report Identifier (IRRID):**

DERR1-10.2196/44318

## Introduction

### Background

In 2013, internet gaming disorder, a syndrome of dysfunctional gaming behaviors that result in distress and affect personal, social, and educational functioning, was included in the appendix of the Diagnostic and Statistical Manual of Mental Disorders, Fifth Edition (DSM-5) [1] as a disorder that needed further research. Although the prevalence of internet gaming disorder is generally low, an increasing number of children who play digital games exhibit problematic gaming behaviors [2], which often result in dysfunctional social behaviors and mental health problems [3]. Delivering high-quality treatment for children with internet gaming disorder is key. This protocol describes a Swedish research project in which we will implement and evaluate an intervention labeled relapse prevention among children at Swedish child and youth psychiatry clinics.

Gaming, or playing offline or online digital games, has received a lot of attention from researchers and professionals in recent years. In Sweden, 68% of Swedish 13-16–year-old children and 55% of 17-18–year-old adolescents play computer games every day [4]. Gaming has become a common everyday arena where children and young people interact and socialize with others. Although some research suggests that gaming could be associated with more positive psychological outcomes, such as a stronger sense of belonging [5] and higher intelligence [6], other studies indicate that gaming can be linked to poor developmental outcomes such as physical and mental illness in adolescence [3]. Indeed, a small proportion of those who play digital games show a problematic development trajectory, similar to that of substance addiction, which is one of the reasons for including internet gaming disorder as an addiction diagnosis in the DSM-5 [1]. The diagnosis is phrased as “a persistent and recurrent use of the Internet to engage in games, often with other players, leading to clinically significant impairment or distress as indicated by five (or more) of the following criteria in a 12-month period: Preoccupation with gaming, withdrawal symptoms when gaming is taken away or not possible (sadness, anxiety, irritability), giving up other activities or continuing to game despite problems” [1]. Although the prevalence of problem gaming and internet gaming disorder in Swedish children and adolescents is to date unknown, a large European study with 12,938 children of 14-17 years of age reports that 5.1% exhibit problem gaming behaviors by fulfilling up to 4 criteria for internet gaming disorder, whereas 1.6% meet all the criteria for internet gaming disorder [7]. As many digital games are aimed at children, whose cognitive development means they are not always well equipped to deal with the instant gratification of most computer games [8], it is expected that problem gaming among children and adolescents will rise.

A development in the clinical management of the more well-established diagnosis of gambling addiction involving money [9,10] has brought attention to the possible association or co-occurrence of gambling, digital gambling, and problem gaming [11], not least given the development of in-game features such as loot boxes, ie, game-related purchases with a chance-based outcome. Moreover, earlier studies suggest that important correlates to child and adolescent problem gaming are male gender [12], neuropsychiatric disorder [13], difficulties with cognitive regulation [14], and substance use [15]. In addition, as parent-child relationships play an important role in child development [16], relationship features such as parent-child bonds and parent-child communication seem to be critical in terms of the development of problem gaming and internet gaming disorder [17]. Children with close parent-child bonds and open parent-child communication could more easily be offered and accept support from their parents, which subsequently could help them control their gaming behaviors. These factors need to be acknowledged both in routine practice as well as in the development of treatment for children and adolescents with problem gaming or internet gaming disorder.

To date, there is no gold standard treatment for children and adolescents with internet gaming disorder. Cognitive behavioral therapy (CBT) is, however, often identified as a first-line treatment for problem gaming, offering patients help with recognizing triggers and cues for gaming, and for understanding and controlling their gaming behaviors [18]. A CBT-based form of treatment, relapse prevention [19,20], has been developed as a treatment for child and adolescent problem gaming and internet gaming disorder. The relapse prevention program, which includes 3 to 8 sessions, has a motivational and relapse-prevention approach [19] where the therapist explores the target, ie, the problem behavior of the individual. Such program is traditionally used as a tertiary (or indicated) intervention strategy, meaning that such preventive effort is used to alleviate the impact of an ongoing problem and to prevent more complications. Relapse prevention treatment is often provided in outpatient clinics, for reducing the likelihood of relapsing into addiction and substance abuse. It is considered among the most effective preventive efforts for substance addiction [20] and works by teaching the individual to identify both internal and external cues to prevent future relapses in similar situations. We hypothesize that by targeting these mechanisms, the treatment could also be effective in treating children and adolescents with problem gaming and internet gaming disorder, because of the similarities of these behavioral addictions to substance addiction.

The effect of an intervention such as relapse prevention could, however, be dependent on the general quality of parent-child relationships and interactions between parents and their adolescent children, such that adolescents with strong family bonds and open parent-child communication would be likely to have more promising outcomes than adolescents with poor family bonds and communication. In that sense, the parent-child relationship could be an important moderator for the effectiveness of an intervention. In addition, given that adolescent development happens in interaction with their environment, such as family and more specifically parents [16], it is also possible that an intervention aimed at adolescents would also have a spillover effect on their environments where parent-child relationships are included. In that sense, not only would the individual benefit from such an effort, but the entire family would as well. Although such ideas seem compelling, they have not been tested in a context of gaming or relapse prevention.

